#### Nutrition Counseling

The dietary advice will be provided by a nutritionist following the Filipino Nutrition Research Institute (FNRI) recommendation called “*Pinggang Pinoy*” or Filipino Plate (56), which is a picture of a 9-inch plate with foods proportionally distributed among the food groups to provide ~1,200–1,500 calories per day. It is advised that half of the plate is composed of green leafy vegetables and one serving of fruit per meal. In general, affordable nutritious food is recommended: high consumption of local fruits and vegetables, brown/purple rice instead of white rice, coconut oil, and other vegetable oils, and fish. General group lectures on healthy diet and individualized counseling for those with identified cardiovascular risks will be done every 3 months. Individualized diet guides developed by FNRI such as high/low caloric, low-sodium, low-cholesterol, and/or diabetes mellitus diet brochures will be provided to the participants depending on their specific needs (available at http://helponline.fnri.dost.gov.ph/help/publications). Diet guides include tips for healthy eating, food selection examples, daily diet plan, and 1-day sample menu. Participants will be asked to use a structured 3-day meal diary for diet monitoring.

#### Vascular Risk Management

After baseline visit (V1), the participants will receive a report on their baseline clinical assessment of vascular risk factors. Participants identified with cardiovascular risks will be examined and advised by study physicians on the management of vascular risks according to standard Filipino clinical guidelines (57–62). When initiation or adjustment of pharmacologic treatment is necessary, participants are given a referral letter to their own physician at the primary health care center for continuity of care. The nurses will monitor participants every month and use a logbook to record their compliance and advise them on a continuing basis. Study physicians and nurses will meet with the participants at the third, sixth, and ninth month to monitor their cardiovascular and metabolic conditions and revise their management plan if necessary. If nurses detect an urgent problem, they will alert participants to see the community physicians.

### Data Processing and Analysis

#### MRI Acquisition

Participants will be scanned in a 3-tesla (3T) MRI scanner (Philips Achieva) using an eight-channel head coil. We will use the Alzheimer's Disease Neuroimaging Initiative (ADNI-3: http://adni.loni.usc.edu/adni-3/) recommended imaging protocols that will allow our data to be comparable with the ADNI centers and good potential for data sharing on open access platforms. A high-resolution 3D T1-weighted sagittal scan/MPRAGE (magnetization prepared gradient echo), and thin T2-weighted and FLAIR (fluid-attenuated inversion recovery) coronal scans are acquired. Functional MRI (task and resting-state) will be collected using a T2^*^ echo-planar imaging (EPI) pulse sequence ADNI-3 Advanced (multiband): TR = 600 milliseconds (ms), TE = 30 ms, flip = 53 degrees, isotropic voxel = 2.5 millimeter (mm), field of view (FOV) = 220 × 220 × 160 mm, 64 slices of simultaneous multi-slice imaging (SMS) = 8 acquired, controlled aliasing in parallel imaging (CAIPI)—shift = 4. Diffusion MRI will be collected using the diffusion tensor imaging (DTI) sequence (multiband): TR = 3,300 ms, TE = 71 ms, isotropic voxel = 2 mm, FOV = 232 × 232 × 160 mm, three shells: b = 500, 1,000, 2,000 seconds/millimeter^2^ (s/mm^2^) (112 total diffusion-weighted directions). The acquisition plane will be rotated 25° with respect to the posterior vertical axis of the brainstem to optimize signal measurements from the cerebellum and neocortices (23). For resting-state fMRI, participants will be asked to keep their eyes open and fixate on a cross (10 min).

For task fMRI, participants will undergo two runs (6–7 min each) of the visual working memory task (Sternberg paradigm) as described by Ng et al. (24) in the scanner (see Figure 1). There will be alternating blocks of high- or low-load conditions, where they will decide whether the “snow flake” at retrieval matches any of those during encoding with a button press. Each cycle consists of one block of high load and one block of low load that had two trials each. Each block is interleaved by a 1.6-s interval and block duration of 20 s. There will be 10 cycles in each run adding up to a total of 20 high-load and 20 low-load trials. Each run lasts 400 s. E-Prime application (version 2.0; PST) will be used.

**Figure 1 F1:**
[figure not shown]
Sternberg visual memory task presented by E-prime in the MRI scanner.

#### Magnetic Resonance Imaging Processing and Analysis

Voxel-based morphometry (VBM8) will be applied for overall brain volumetric analysis with the high-resolution MPRAGE T1-weighted image acquired. Tract-Based Spatial Statistics (TBSS) will be applied to diffusion MRI preprocessed with the FMRIB Software Library (FSL) for understanding changes in structural connectivity. The high-resolution MPRAGE scan will also be applied for automated hippocampal volumetric studies using NeuroQuant. The axial thin T2-weighted and FLAIR will be coronal scans that are used for detecting subcortical and deep white mater hyperintensities (WMH). fMRI data will be preprocessed and analyzed using the Statistical Parametric Mapping (SPM-12) software package. All structural and functional images will be reoriented before the EPI data is preprocessed using the conventional procedure in three phases. In phase one, slice timing correction will be corrected to the timing of the middle slice, realignment to the first volume, and coregistration of the structural images to functional images. In phase two of the preprocessing, flow fields are created before the images are smoothed with a Gaussian kernel of 5-mm full width at half maximum (FWHM) and normalized to the Montreal Neurological Institute (MNI) template. Thereafter, first-level analysis (individual statistics) will be computed using the general linear model. This is followed by the second-level analysis (group statistics) in which a random-effect one-sample *t*-test will be applied on all participants in each group to obtain the group activation map. For resting-state data, we will employ a data-driven empirical approach using the group-independent component analysis (GIFT software) to extract the resting-state components, as well as the seed-based approach using functional connectivity software (CONN) toolbox and SPM12 for second-level group analyses. Regions of interest (ROI) analyses will also be conducted. Percent signal change from fMRI maps will be extracted from significant regions to conduct correlational analyses with the cognitive measures (EFC, MST). Similarly, these cognitive measures will also be correlated with the fractional anisotropy (FA) values extracted from the skeletal map from TBSS.

#### Data Management and Statistical Analysis

Data will be encoded independently by two research associates, and inconsistencies will be double checked with the data source to ensure data accuracy. All tests (primary and secondary outcomes) will be analyzed as independent continuous measures; additionally, we will also analyze for executive function composite (EFC) score derived by dividing independent test scores with their maximum possible scores and summing across tests for EFC, as was done in previous studies (63–65).

The study will employ univariate, bivariate, and multivariate statistics. For univariate, descriptive statistics (mean/SD; frequencies/percentages) will be used to summarize sociodemographic and other baseline characteristics. The bivariate analyses that examine underlying relationships between the outcomes and other clinical characteristics are the following: independent *t*-test for continuous variables and Chi square test (or Fisher exact test when ≤ 20 of the cells have the expected count <5) for categorical variables to compare baseline data between the intervention and control groups. Pairwise comparison of the randomization groups per timepoint will also be done to explore differences at different times using independent *t*-test. For multivariate analyses, the study would estimate the effect from baseline to follow-up at 12 months between randomization groups. Since the participants will be assessed three times (at baseline, 6th and 12th months), the study will be using multilevel mixed models to test the significance between group means but controlling for possible confounders (i.e., when age, sex, and education were not successfully controlled for in the randomization design). Necessary diagnostics will also be considered. This multilevel model is appropriate as it can take into account the clustering effect, and the number of clusters in this study is moderately sized (25–30 clusters per arm).

To analyze for the secondary outcomes, RM-ANOVA/RM-ANCOVA will also be used. Point estimates and their corresponding confidence intervals will be evaluated to assess precision and power. Very wide confidence intervals will signify underpowered analyses. Sensitivity analysis will be conducted including imputation of missing data using last observation carried forward or mean imputation. Data management will primarily be the responsibility of the research team. All data will be securely stored and accessible only to the researchers in compliance with the ethics approval of the study.

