### Sample Size Determination

Sample size was calculated based on the results of quasi-experimental study for INDAK where we compared the mean difference in ADAS-Cog, the primary outcome, from baseline and after 1-year follow-up between intervention and control groups. In that study, ADAS-Cog decreased by 3.16 (SD = 5.97) in the intervention group and 0.91 (SD = 8.69) in the control group (15), with an α error of 5% and β of 5% (power of 95%), and a one-tailed alternating hypothesis in favor of the intervention group, the sample size calculated is 136 per group or 272 for two groups (intervention and control). To account for clustering, a design effect of two will be adopted. This means that the total sample will be 544, with 272 participants per group. Allowing for 10% dropout, the final total sample size required in this study is 605 participants. This will be divided into 20–25 clusters per treatment arm. One cluster will have 12–15 participants, a range we found to be optimum for the intervention in the previous observational study. For MRI, at least 20% of the sample will undergo MRI, selected randomly from both intervention and control arm. This will be proportionally allocated to both arms. The estimated pilot size is 60 participants or 30 per group, expecting higher dropouts; 20% allowance was added giving a final pilot size of at least 72 or 36 per group. The pilot phase is to assess the acceptability of combined interventions (i.e., INDAK, vascular risk management, and nutrition counseling), determine adherence and dropout rates, as well as identify challenges and feasibility of conducting and advancing our research findings with neuroimaging outcomes.

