### Randomization and Allocation Concealment

Cluster randomization will be used to ensure blinding and avoid contamination of group allocation (33), which was one of the challenges in the quasi-experimental study for INDAK (15). The rationale behind this design is to ensure sociocultural fitness of study to the close-knit and socially collective nature of the Filipino community. Communities are “*barangays*,” the smallest government unit in the Philippines, which is mostly characterized by a high population density (1). People live close to each other, acquainted and frequently interact with one another. They share the same public space and health services (e.g., health center, social center), therefore individual randomization within the same community will limit opportunity of concealing treatment allocation. A barangay is referred to as one cluster in this study.

Randomization will be done after baseline assessment is completed (V1); hence, allocation is concealed to the assessors. Clusters will be randomized to a 1:1 ratio by the study statistician using a computer-generated randomization method, constrained using minimization. That is, each community will be allocated with a probability of 0.8 to the group that minimizes the imbalance at baseline of the means of the primary outcomes. The study statistician will inform the primary investigator of group allocation, and the study coordinator will arrange the delivery of intervention. The outcome assessors will be blinded to group allocation. Their engagement with the participants will be limited only to the day of assessment.

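### The primary model adjusts for age, sex and education only if they turn out unbalanced, although the minimisation never uses them, and it does not name the minimised baseline scores as covariates

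*Protocol article*

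**What the plan says.** All references are to the protocol article. Under Data Management and Statistical Analysis the primary analysis is longitudinal: "Since the participants will be assessed three times (at baseline, 6th and 12th months), the study will be using multilevel mixed models". Its target is given as follows: "the study would estimate the effect from baseline to follow-up at 12 months between randomization groups". Covariates are handled by one clause, which describes the model as "controlling for possible confounders (i.e., when age, sex, and education were not successfully controlled for in the randomization design". No baseline outcome score is listed as a covariate.

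Under Randomization and Allocation Concealment, the balancing method is minimisation of clusters. The favoured arm is described as "the group that minimizes the imbalance at baseline of the means of the primary outcomes". A cluster goes to that arm with probability 0.8, not with certainty. No other balancing factor is named.

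The analysis section also plans t-tests and chi-square or Fisher tests "to compare baseline data between the intervention and control groups". It does not say that these tests decide which covariates enter the model.

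**The concern.** The two sections do not fit together. The covariate clause presumes that the randomisation is meant to control age, sex and education, but the minimisation does not use them. Whether they enter is left to a judgement made after baseline data are seen, with no threshold and no named decision-maker. The protocol itself treats two of the three as prognostic: Outcome Measures describes the ADAS-Cog norms as stratified by age and education. Prognostic covariates are worth adjusting for whatever the chance balance.

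The variables that do determine allocation, the baseline scores, are not named as covariates. After minimisation, a standard error reflects the balance achieved only if the analysis takes account of the balancing factors. At stake are discretion over the primary estimate and precision that the trial has already paid for.

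**Working it through.** The protocol gives no figure on this point, so there is none to reproduce. The check has four steps.

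**1. Sections side by side.** Factors in the minimisation: baseline means of the primary outcomes. Factors in the conditional clause: age, sex, education. The lists do not overlap. Criterion for the condition: none stated.

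**2. What the unstated model form implies.** With complete data, a model with group, visit and group-by-visit terms and a free baseline mean in each arm gives a 12-month contrast equal to the difference in mean change. Constraining the arms to a common baseline mean gives roughly the baseline-adjusted (ANCOVA) contrast. The protocol does not say which is meant. The sample size is built on change ("ADAS-Cog decreased by 3.16 (SD = 5.97) in the intervention group and 0.91 (SD = 8.69) in the control group"), which makes the change form plausible but does not settle it.

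With equal variance s² at both times and correlation rho:
- change: 2s²(1 − rho)
- baseline-adjusted: s²(1 − rho²)
- ratio: (1 + rho)/2

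The documents give SDs of change but no SD of the score itself, so rho cannot be derived and is assumed.

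| rho (assumed) | change / s² | adjusted / s² | variance ratio | SE ratio |
|---|---|---|---|---|
| 0.5 | 1.00 | 0.75 | 0.75 | 0.87 |
| 0.7 | 0.60 | 0.51 | 0.85 | 0.92 |
| 0.8 | 0.40 | 0.36 | 0.90 | 0.95 |

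**3. Effect of the minimisation.** Simulation of cluster means: 44 clusters of 12, assumed ICC 0.08, one outcome, two-sided 5% test, 4,000 runs per scenario. Each cluster went with probability 0.8 to the arm giving the smaller between-arm difference in summed baseline cluster means. Correlations (cluster / participant level) and the effect of 0.25 SD are assumptions.

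| Correlation | Type I, change | Type I, adjusted | Power, change | Power, adjusted |
|---|---|---|---|---|
| 0.5 / 0.5 | 2.8% | 5.1% | 52% | 65% |
| 0.7 / 0.7 | 3.8% | 4.9% | 76% | 81% |
| 0.9 / 0.8 | 4.0% | 4.7% | 96% | 97% |

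Monte Carlo standard error at 5% is √(0.05 × 0.95 / 4000) = 0.34 percentage points.

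Under the null, the spread of the two estimates hardly differs: 0.1058 against 0.1044, 0.0865 against 0.0859, and 0.0639 against 0.0637. In variance terms the ratios are about 0.97, 0.99 and 0.99. The minimisation has already removed most of the baseline noise. The ratio in step 2 therefore mainly describes the variance that the analysis reports: the change analysis reports a standard error that is too large.

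**4. Chance entry of covariates, only if 5% baseline tests were the trigger.** With three independent tests and no clustering, at least one flags in 1 − 0.95³ = 14.3% of trials. If a design effect of 2 applied to all three covariates and the tests ignored it, each would flag with probability 2[1 − Φ(1.96/√2)] = 0.166, and at least one in 1 − (1 − 0.166)³ = 42%. The protocol adopts the design effect of 2 for the sample size and gives no clustering figure for age, sex or education.

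**The case against.** The condition can be read as ordinary language for adjusting if chance imbalance remains. Randomisation balances unlisted factors on average, and minimising on cognitive scores may balance age and education indirectly. That reading is fair, but the rule is still contingent on the data and still lacks a criterion.

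A condensed article may also leave the covariate list and model form to an analysis plan that is not shown. That stands for details such as the random-effects structure. It does not cover a rule the article does state and that does not match its own design.

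Three stronger readings are tempting and not supported:
- A reader might infer that the baseline significance tests choose the covariates. The article plans those tests but never links them to the model, so the 14% to 42% range is conditional.
- A reader might infer that baseline is ignored. It is one of the three modelled assessments, and the effect is measured from baseline.
- A reader might infer a serious error-rate problem. The simulation does show 0.1% to 2.6% type I error for an analysis of follow-up scores alone, but the protocol does not plan that analysis.

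The gain also shrinks as correlation rises. The power gap falls from 13 points to 1, and at the test–retest coefficient of 0.93 quoted for ADAS-Cog the variance ratio would be (1 + 0.93)/2 = 0.965. That figure is a reliability, not a 12-month correlation in this population, but it shows the direction.

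The Fisher rule ("Fisher exact test when ≤ 20 of the cells have the expected count <5") has its inequality the wrong way round and lacks a percent sign. It is a wording slip in a baseline table and changes no primary result.

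**Conclusion.** The point holds as a flaw in how the primary model is fixed. Adjustment for age, sex and education is contingent on observed balance, without a criterion, and refers to a control that the minimisation does not provide. The minimised baseline scores are not named as covariates, and how baseline enters is left open.

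The size is moderate. If a change contrast is fitted, type I error is about 2.8% to 4.0% against a nominal 5%, and reported variance is higher than necessary, with a ratio of 0.75 to 0.90 for correlations of 0.5 to 0.8. These figures rest on an assumed ICC, correlations and effect size, and on a simplified single-outcome minimisation. If the model already constrains baseline to be common, most of this loss disappears and only the contingent covariate rule remains. Nothing here shows bias or an inflated false-positive rate. The case for change is lost precision and avoidable analyst discretion.

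**What to change.** Delete the conditional clause and specify the primary model in advance:
- age, sex and education as covariates whatever the observed balance;
- the participant's baseline score of the outcome and the cluster baseline means used in the minimisation, with months 6 and 12 as outcomes; or, alternatively, a longitudinal model with the arms constrained to a common baseline mean;
- random effects for barangay and participant.

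Describe baseline by arm without significance tests, or at least state that such tests do not select covariates.

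The cost is analysis wording plus a few degrees of freedom. Cluster means of three primary outcomes use three cluster-level degrees of freedom, out of 38 to 48 with the 40 to 50 clusters implied by Sample Size Determination (clusters minus two). The schedule in Table 1 already collects every variable. The article reports eight clusters randomised and recruitment paused, so the change can be made before the main trial resumes.

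### As stated, RM-ANOVA/RM-ANCOVA for the secondary outcomes and the per-visit t-tests ignore randomisation by barangay, and no rule says the multilevel model prevails

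*Protocol article*

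**What the plan says.** The Randomization and Allocation Concealment section fixes the unit of allocation: "A barangay is referred to as one cluster in this study", and "Clusters will be randomized to a 1:1 ratio by the study statistician". Sample Size Determination states "To account for clustering, a design effect of two will be adopted" and gives the cluster size: "One cluster will have 12–15 participants".

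The section on Data Management and Statistical Analysis names three ways to compare the arms:

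- A multilevel mixed model for the effect from baseline to 12 months, defended on the ground that it allows for clustering. The text does not confine it to the primary outcomes.
- Per-visit tests, listed under the bivariate analyses: "Pairwise comparison of the randomization groups per timepoint will also be done to explore differences at different times using independent" t-tests.
- For the secondary outcomes: "To analyze for the secondary outcomes, RM-ANOVA/RM-ANCOVA will also be used".

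No cluster term, cluster-level summary or variance correction is attached to the second or third method. The section does not say which method prevails when two apply to the same outcome.

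**The concern.** Repeated-measures ANOVA or ANCOVA models the correlation between visits of one person. It treats two people from the same barangay as independent. The independent t-test does the same. In this trial people in a barangay share an allocation, a health centre and, in the intervention arm, dance sessions and group lectures. The protocol's own case for cluster randomisation is that residents live close together and interact often, which is a reason to expect correlated outcomes.

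A between-arm test that ignores positive correlation within clusters uses standard errors that are too small. At stake are claims of benefit on GDS, EQ-VAS and BBS, and the per-visit comparisons. The plan also intends to judge power from the width of its confidence intervals, and intervals that ignore clusters would make that check look better than it should.

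**Working it through.** **The plan's own figures.** 136 per group × 2 groups × design effect 2 = 544, and 544 / 0.90 = 604.4, rounded up to 605. So the design effect of 2 does enter the final sample size. (The starting figure of 136 corresponds to 80% power at a one-sided 5% level; the stated 95% gives 238. That is a separate matter and does not alter what follows.)

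**Implied ICC.** The protocol gives no ICC. From DE = 1 + (m − 1) × ICC with DE = 2, ICC = 1/(m − 1). That is 1/11 = 0.091 for m = 12 and 1/14 = 0.071 for m = 15.

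**Type I error of a simple two-arm test that ignores clusters.** The true standard error is √DE times the reported one, so the actual error is 2 × [1 − Φ(1.96/√DE)] two-sided, or 1 − Φ(1.645/√DE) one-sided. At DE = 2, √2 = 1.41:

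- two-sided: 2 × [1 − Φ(1.386)] = 16.6%, or 3.3 times nominal;
- one-sided: 1 − Φ(1.163) = 12.2%, or 2.4 times nominal;
- reported intervals have 1/1.41 = 0.71 of the correct width, so they are about 29% too narrow.

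Only the sample size is stated to be one-tailed. The sidedness of these tests is not given, so both figures are shown.

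**Range.** The ICCs of the secondary outcomes are not in the document. Assuming 0.01 to 0.10:

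| m | ICC | DE | Two-sided error |
|---|---|---|---|
| 12 | 0.01 | 1.11 | 6.3% |
| 12 | 0.05 | 1.55 | 11.5% |
| 15 | 0.05 | 1.70 | 13.3% |
| 15 | 0.10 | 2.40 | 20.6% |

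**MRI.** At least 20% of 605 is 121 people. Sample Size Determination says "This will be divided into 20–25 clusters per treatment arm", so 40 to 50 clusters in all, and 121/50 = 2.4 to 121/40 = 3.0 scans per cluster if they are spread evenly. At the implied ICC of 0.071 to 0.091 the DE is 1.10 to 1.18 and the two-sided error 6.2% to 7.2%. The analysis section instead says "the number of clusters in this study is moderately sized (25–30 clusters per arm"); more clusters would mean fewer scans in each, and less inflation. The figure rests on the 20% subsample. The Baseline Assessment section can be read as MRI for everyone, in which case the larger cluster sizes above would apply.

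**RM-ANOVA specifically.** The formula above is for a simple comparison of two arms. RM-ANOVA gives a group main effect and a group-by-time test, which behave differently. A simulation with no treatment effect used 20 clusters per arm, 14 people per cluster, three visits, an assumed total ICC of 0.08 (DE = 1 + 13 × 0.08 = 2.04) and 2000 runs. The Monte Carlo error at 5% is √(0.05 × 0.95/2000), about 0.5 percentage points. Rejection rates at a nominal 5%:

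| Cluster effect | 12-month t-test | RM-ANOVA group effect | RM-ANOVA group-by-time |
|---|---|---|---|
| Constant over visits | 18% | 22% | 4.6% |
| Half varies by visit | 17% | 17% | 25% |
| All varies by visit | 17% | 12% | 35% |

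The t-test and the group main effect are inflated in every row. The group-by-time test is not inflated when cluster effects are constant, and is strongly inflated when they vary between visits.

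**The case against.** The best defence is that a cluster-aware analysis of the secondary outcomes is already planned. The section opens by covering primary and secondary outcomes together, names the multilevel model without restricting it, and only then says that RM-ANOVA will *also* be used. The t-tests are presented as exploratory, while the 12-month effect is assigned to the multilevel model. This reading is fair and cannot be excluded. It narrows the defect but does not remove it: the secondary outcomes would then have two analyses, one of them inconsistent with the design, and no stated order between them. An exploratory label lowers the weight of a t-test but does not correct its standard error.

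A reader might infer that false positives are tripled for every secondary outcome. The document does not support that. The design effect of 2 was adopted for ADAS-Cog, no ICC is given for any other outcome, and a low ICC gives only mild inflation. Tripling also fails for the MRI subsample, and it is not a general property of the group-by-time test. On that last point one counterweight stands: the sample size rests on change from baseline to one year, so the plan itself allows for clustering of change in ADAS-Cog.

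A reader might also infer that all per-visit t-tests are inflated alike. Allocation is minimised on the baseline means of the primary outcomes, so the formula cannot be assumed for those outcomes at baseline. Finally, one might infer that the primary result is compromised. It is not, because it rests on the multilevel model.

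**Conclusion.** The point holds in a limited form. Two of the three between-arm methods named in the protocol do not, as stated, reflect the unit of randomisation, and this conflicts with the protocol's own design effect and its own reason for choosing the multilevel model. This concerns what the protocol names, so a more detailed analysis plan would have to override it and not merely fill a gap.

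The size is conditional. If DE = 2 carried over to GDS, EQ-VAS and BBS, a follow-up comparison ignoring clusters would have about 16.6% two-sided or 12.2% one-sided error. Under the assumed ICC range the two-sided figure could be as low as about 6% or as high as about 21%. For MRI the effect is small if about 20% are scanned. For the RM-ANOVA group-by-time test it depends on an unstated quantity, the variation of cluster effects over time. The primary multilevel analysis is unaffected, so the risk lies in the secondary and per-visit claims.

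**What to change.** State that the multilevel mixed model already named, with random effects for barangay and participant and a group-by-visit term, is the inferential analysis for every secondary outcome. Take the 6- and 12-month between-arm contrasts from that model. Either drop RM-ANOVA/RM-ANCOVA and the between-arm t-tests, or keep them as descriptive summaries without p-values or confidence intervals.

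When the random part is specified in detail, consider letting the barangay effect differ between visits. The simulation shows that this variation drives the error of the group-by-time test, and a barangay intercept that is constant over time would not absorb it.

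The cost is wording only. No design change or extra data are needed, and the article reports recruitment paused after eight clusters. Confidence intervals for the secondary outcomes will be wider: by a factor of about 1.41 for a simple between-arm contrast if the design effect is 2, and by less if it is smaller.
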